### Sample Size

We aim to include *N* = 200 participants, allowing for a between-trial arm group comparison against a statistically relevant effect size threshold of *d* = 0.40, a power (1 − β) of 80%, and an alpha of 0.05 (two-tailed) for the intention-to-treat (ITT) analysis (54). A recent meta-analytic review for Internet-based stress interventions reported effect sizes of *d* = 0.64 for perceived stress in guided interventions but considerably smaller effect sizes for unguided programs (*d* = 0.34 for depression, *d* = 0.32 for anxiety) (27). Results for Internet-based interventions addressing psychological distress in tertiary education are mixed, ranging from non-significant findings to moderate-sized effects in favor of the respective intervention (55–59). Thus, we aim for an effect size of *d* = 0.40.

### Intervention Platform

The technology platform used to deliver the intervention in the IG as well as the psychoeducational material in the CG is provided by Minddistrict. This company is responsible for the provision and maintenance of the platform. Its content management system is used to upload interventions, add participant and eCoach profiles, and fill out questionnaires. The platform conforms to all required quality standards and operates according to the ISO 27000 and NEN 7510 norms. All data are securely stored on ISO 27000 certified servers and transmitted using HTTPS with SSL certificates (AES-256 and SHA-1, 2048-bit RSA). Unauthorized access to the platform is not possible.

### Intervention

This trial will evaluate the *StudiCare Fernstudierende* intervention. It was adapted from *StudiCare Stress* (32), an Internet- and App-based intervention for college students. A detailed description of this pilot program can be found elsewhere (32, 60). Together with the preceding pilot intervention, the program is based on *Get.On Stress*, an Internet-based stress intervention for employees (36, 37), which was adapted to a university student context.

In terms of therapeutic content, *StudiCare Fernstudierende* only marginally deviates from *StudiCare Stress*. To tailor the intervention to distance-learning students’ needs, one new student testimonial is introduced and will lead participants through the intervention. The testimonial represents an elder student with children. The testimonial was created to address the specific problems of non-traditional distant-learning students, such as limited time for studying, having to take care of children, or facing financial pressure.

Conceptually, the Internet intervention aligns with Lazarus’ transactional model of stress (61). It adheres to a two-component structure, incorporating problem- and emotion-focused coping through emotion regulation strategies. In problem-focused coping, cognitive behavioral strategies are applied to solve personal problems and to reduce and eliminate stressors (62). Emotion regulation refers to processes through which individuals monitor, evaluate, and modify emotions to reach relevant goals (63).

There are various stressors in university students’ lives that might be potentially solvable by applying problem-solving strategies. Problem-solving heuristics have been shown to be a practical method for addressing stressors and have been proven to be effective in improving mental health outcomes (64, 65).

To tackle situations in which problem-focused strategies are inapplicable, emotion regulation techniques may be employed to control negative emotions associated with unsolvable problems. Current findings indicate that deficits in the ability to detect and regulate negative emotion may contribute to the wellbeing of individuals, as well as the development and trajectory of mental disorders (66–69). Emotion regulation strategies have shown to be an adequate therapeutic instrument in alleviating various symptoms of mental illness (70–72).

The intervention contains seven modules, each of which can be completed in one session (see **Table 1**). Completing one session is estimated to take about 30–90 min, and participants will be advised to work on one or maximum two modules per week. The intervention is therefore intended to last about 5–7 weeks. After modules 2–7, participants will be offered optional add-on mini-modules. These mini-modules cover information and exercises on student-specific topics of interest: social support, rumination and worrying, time management, procrastination, test anxiety, sleep, motivation, nutrition and exercise, dealing with writer’s block, and concentration. An additional booster session allowing participants to recap and rehearse previously learned strategies will be offered 2 weeks after completion of the main modules. Therapeutic content is presented as an illustrative story of a backpacking trip around the world, with each module representing a new continent.

**Table 1 T1:** Modules of the intervention (StudiCare Fernstudierende).

Session	Name	Content	
1	Introduction	Psychoeducation, information about stress and preview of subsequent sessions	
2	Problem-solving	Stress management strategies, systematic problem-solving using a 6-step problem solving heuristic	
3	Muscle and breath relaxation	Information on basic principles of muscle and breath relaxation, audio exercises for daily usage	
4	Mindfulness	Coping with self-criticism, mindfulness exercises	
5	Acceptance and tolerance	Dealing with unsolvable problems, psychoeducation on and exercises for acceptance and tolerance of unpleasant emotions	
6	Self-compassion	Self-criticism in precarious situations, defusion of self-worth and performance, exercises for positive self-support, overcoming dysfunctional perfectionistic thought-action patterns	
7	My master plan	Recognizing physiological warning signs, creating a plan for the future	
8	Booster session	Further information on self-help and psychotherapy, evaluation of training transfer, recap of all sessions, repetition of previous exercises	
2–7	*Elective mini-modules*	*Social support*	communication styles, receiving and providing support
		*Rumination and worrying*	reflection on positive and negative aspects of worry, coping with uncertainty
		*Time management*	effective time scheduling, common planning fallacies, learning to prioritize
		*Procrastination*	identifying situations in which procrastination occurs, strategies to reduce procrastination
		*Test anxiety*	effective studying techniques, using paradoxical intentions, de-catastrophizing blackouts
		*Sleep*	sleep restriction
		*Motivation*	finding reasons for lacking motivation, exercising delay of gratification
		*Nutrition and exercise*	creating an individual eating and exercise schedule, dealing with relapses
		*Dealing with writer’s block*	reasons and mechanisms for writer’s block
		*Concentration*	audio-based concentration exercises

Some technical features were added to strengthen the transfer of intervention content into participants’ everyday life. Homework assignments are given after every module to practice techniques presented during the session. To keep track of mood fluctuations and describe experiences in transferring acquired knowledge, a personal diary App is introduced in the first lection and can be downloaded afterward. After every module, audio files and module summaries can be accessed, containing exercises to be worked on until the next session.

### Psychoeducation

Participants in the active CG will receive psychoeducational information about cognitive, emotional and physical determinants, symptoms, and outcomes of psychosocial stress in general and with respect to distance-learning students. The psychoeducation lessons are delivered through the same platform as the intervention in the IG. In contrast to the intervention, the psychoeducation lessons are largely text-based and do not contain any interactive components. In line with the weekly intervals of the IG, the psychoeducation consists of seven main sessions and one booster session, and is designed to be completed within 5–7 weeks. An overview of the psychoeducation material provided in each module is presented in **Table 2**.

**Table 2 T2:** Psychoeducation modules in the control group.

Session	Name	Content
1	Introduction	Prevalence and types of stress; biological response to stress; effects of stress on emotions, thought, somatic symptoms
2	Causes of stress	Common stressors among students; Lazarus’ transactional model of stress
3	Does stress have the same effect on all individuals?	Short and long-term consequences of stress; inter-individual differences in stress response
4	What effect does stress have on the body?	Physiological response to stressors; evolutionary background of stress reactions; stress and performance
5	Cognitive appraisal	Common dysfunctional thoughts contributing to perceived stress; 5 steps for cognitive reappraisal
6	Coping and resources	Typical resources and coping mechanisms for stress
7	Health	Definition of health and sense of coherence
8	Booster session	Recap of previous material

### Guidance

In order to support participants in adhering to the intervention while minimizing human capital costs, we will apply an adherence-focused guidance concept with personalized feedback on demand [for a detailed description of an application, see Refs. (38, 73, 74)]. The supportive accountability model suggests that the adherence and effectiveness of Internet-based interventions are enhanced by providing a minimum of human support by a professional seen as benevolent and competent by participants (75, 76). The guidance concept for this study was developed in line with these core elements.

Guidance for the IG will be performed by a specially trained student in a master’s program in psychology and consists of three parts: i) monitoring adherence to the intervention, ii) sending standardized motivational messages after every module, and iii) providing feedback on demand. Adherence monitoring involves personal reminders for participants who had not completed a session in the designated timeframe (7 days). Standardized motivational messages tailored to each session will be sent when participants completed one of the main modules, summarizing the content of the previous module and motivating trainees to stay engaged. Feedback on demand will be provided through the internal messaging system of the training platform, which participants may use whenever individualized content feedback is needed. Participants will then receive feedback within 48 h. If requested, participants in the IG will be able to receive automatic messages containing short, motivational prompts *via* SMS.

Participants in the active CG will receive parts (i) and (ii), but will not receive feedback on demand.

### Primary Outcome

The primary outcome is symptoms of depression as measured by the German version of the CES-D 20-item version [ADS (51); 20 items; range 0–60] at post-treatment (T1). Participants will be asked to indicate the frequency of depression-specific symptoms for a retrospective timeframe of 2 weeks on a four-point Likert scale [0 = *rarely or none of the time present* (less than 1 day), 3 = *most of the time present* (5–14 days); e.g., “During the past two weeks I had trouble keeping my mind on what I was doing.”]. Higher scores indicate greater depression severity. The CES-D shows high correlations up to *r* = 0.90 with other measures such as the Hamilton Depression Scale or the Beck Depression Inventory, and has a high retest reliability of *r*
*_tt_* = 0.81, indicating the high internal validity of this instrument (51).

### Secondary Outcomes

The number of items and range of below-mentioned instruments is reported in parentheses. Unless otherwise specified, all outcomes will be measured for a retrospective timeframe of 2 weeks. For a comprehensive overview of all variables, see **Table 3**.

**Table 3 T3:** Overview of instruments and assessment points.

Variable	Instrument	T0	T1	T2	Putative moderator

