**Secondary outcomes**					
*Mental health*					
Perceived stress	PSS-10	X	X	X	–
Anxiety	STAI-6	X	X	X	–
Worrying	AWQ	X	X	X	–
Emotional exhaustion	MBI-S	X	X	X	–
Behavioral activation, rumination	BADS	X	X	X	–
*Academic outcomes*					
Work impairment, productivity	PSS	X	X	X	–
College self-efficacy	CSEI	X	X	X	X
*Risk and protective factors*					
Emotion regulation skills	SEK-27	X	X	X	X
Resilience	CD-RISC	X	X	X	–
Self-compassion	SCS	X	X	X	–
Locus of control	IE-4	X	–	–	X
Self-esteem	RSES	X	X	X	–
Beliefs about stress	BASS	X	X	X	X
*Health economic measures*					
Indirect costs	TiC-P	X	X	X	–
*Health literacy and help-seeking behavior*					
Help-seeking intentions	GHSQ	X	–	–	–
Internet therapy experience	–	X	–	–	–
E-Health literacy	eHEALS	X	–	–	–
Reasons for participation	–	X	–	–	–

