*Modifiable risk and protective factors*. Risk and protective factors for mental illness include resilience as measured by the Connor-Davidson Resilience Scale short form [CD-RISC (89); 2 items; range 0–8], emotion regulation competencies [German version of the Assessment of Emotion Regulation Skills; SEK-27; State Version (90); 27 items; range 27–108], self-compassion [Self-Compassion Scale; SCS-D (91); 12 items; range 12–60], self-esteem as measured by the Rosenberg Self-Esteem Scale [RSES (92); 10 items; range 10–40], and locus of control as measured by the Short Scale for the Assessment of Locus of Control [IE-4 (93)]. The IE-4 consists of two subscales for internal and external locus of control, each consisting of two items (range 2–10). Personal beliefs about the controllability and the harmful and positive nature of stress will be assessed using the Beliefs about Stress Scales’ [BASS (94)] subscales for positive (four items; range 4–16), negative (eight items; range 8–32), and controllability beliefs (three items; range 3–12).

*Health economic measures*. Indirect costs due to presenteeism and absenteeism will be assessed using the productivity loss subscale of the Trimbos/iMTA questionnaire for costs associated with psychiatric illness [TiC-P (95)], which was adapted to the context of distant-learning students in tertiary education. With this questionnaire, participants register approximations of their working hours at university, household work, and monthly salaries when holding a job besides their studies. Indirect costs, such as the number of “work loss” days (absenteeism from work) or the number of “work cut-back” days (reduced productivity at work), can be assessed.

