*Moderators of treatment effects*. To assess the effect of putative moderators on changes in outcomes (i.e., T0 – T1), an ordinary least squares (OLS) regression-based framework for estimating interactions in moderation models will be used, along with simple slopes for probing interactions. In order to test the robustness of our findings and to examine differences between imputed data and complete cases, separate sensitivity analyses (109, 110) will be conducted. Moreover, to assess relevant subgroup effects, follow-up simple slope analyses for possible significant interaction effects will be conducted. The slope and significance of the intervention main effect will be evaluated for conditional values (one standard deviation below and one standard deviation above the mean) of the moderator (111). For more precise information on conditional effects of the moderators, the Johnson–Neyman technique will be applied (112).

*Cost–benefit evaluation*. According with common practice, a probabilistic approach will be used to make health-economic inferences (113). The total benefit of the intervention will be derived by subtracting productivity loss costs assessed by the TiC-P of the CG from the ones of the IG. The cost–benefit relationship will be reported by calculating the three most frequently used metrics: i) the net benefits (NB), the net monetary gain of the intervention; ii) the benefit–cost ratio (BCR), the money saved for one monetary unit invested; and iii) the return-on-investment (ROI), indicating the percentage of profit with every monetary unit invested. Bootstrapped 0.95% CIs with 2,500 replications will be estimated around these metrics.

Sensitivity analyses will be conducted to assess the robustness of the findings and to account for uncertainty regarding the actual prize of implementing the intervention into health care. Further health economic analyses will be conducted if feasible.

*Help-seeking behavior analysis*. To make assertions on the help-seeking intentions and behaviors of participants, baseline data of all participants from the GHSQ-Per-Emot (96), eHEALS (97), “awareness of online counseling,” and “reasons for participation” questionnaires will be analyzed using descriptive statistics.

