## Abbreviations

CG, control group; CONSORT, Consolidated Standards of Reporting Trials; IG, intervention group; ITT, intention to treat; RCI, Reliable Change Index; RCT, randomized controlled trial; SPIRIT, Standard Protocol Items: Recommendations for Intervention Trials; T0, baseline; T1, post-assessment (7 weeks after randomization); T2, 3-month follow-up (3 months after randomization).

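### The cost–benefit formula leaves out the baseline TiC-P cost that the trial collects, so net benefit, BCR and ROI are less precise than they need be

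*Protocol article*

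**What the plan says.** Under Secondary Outcomes, in the text on health economic measures, the article states: "Indirect costs due to presenteeism and absenteeism will be assessed using the productivity loss subscale of the Trimbos/iMTA questionnaire". It adds that "participants register approximations of their working hours at university, household work, and monthly salaries" where a job is held. Table 3 has the row "Indirect costs TiC-P X X X", meaning T0, T1 and T2.

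Under Statistical Analyses, the cost–benefit evaluation defines the estimator: the total benefit is obtained by "subtracting productivity loss costs assessed by the TiC-P of the CG", with the corresponding IG costs as the figure subtracted from. Three metrics follow: "the net benefits (NB), the net monetary gain of the intervention", the benefit–cost ratio (BCR) and the return on investment (ROI), with bootstrap intervals from 2,500 replications. No baseline term appears.

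The clinical evaluation in the same section handles change between arms by analysis of covariance with the baseline score as covariate.

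On timing, Secondary Outcomes opens with a general rule: "Unless otherwise specified, all outcomes will be measured for a retrospective timeframe of 2 weeks". The text on the TiC-P gives no recall period of its own. T1 is 7 weeks after randomisation, and the Abbreviations define T2 as "3-month follow-up (3 months after randomization").

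**The concern.** Productivity costs built from hours and salaries differ greatly and persistently between people. The Background describes a population that mixes employees, parents and older students. Someone with a high salary and many lost hours at T0 is likely to have high costs at T1 and T2 whichever arm they are in. The T0 cost should therefore predict the later cost, and a formula that leaves it out keeps that predictable variation in the error term. It also lets a chance difference between arms at T0 carry over in part into the estimated benefit.

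All three metrics are functions of this one benefit figure, so all three inherit the loss. Health-economic benefit is the fourth stated goal of the trial, and the Discussion admits that power for economic inference is limited. That makes it hard to justify giving up precision that data already scheduled would provide.

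**Working it through.** **Design figure.** The article gives no figure for the precision of costs. Its only design figure is N = 200 for d = 0.40, 80% power and two-sided alpha 0.05. The normal approximation gives n per arm = 2 × (1.960 + 0.842)² / 0.40² = 98.1, rounded up to 99, or 198 in total. The t-test version gives 99.1, hence 100 per arm and 200 in total, with 80.4% power. The stated N reproduces, and 100 per arm is used below.

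**Inputs.** n = 100 per arm (Sample Size; 1:1 allocation). Correlation r between T0 cost and post-randomisation cost: not given, so assumed at 0.3, 0.5 and 0.7. Costs are in SD units, with the same SD in each arm.

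**Raw difference.** SE = √(2/100) = 0.141 SD. The 95% half-width is 1.96 × 0.141 = 0.277 SD.

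**Adjusted difference.** Variance is multiplied by 1 − r², so the half-width is 0.277 × √(1 − r²). The raw interval is wider by 1/√(1 − r²) − 1. The equivalent unadjusted sample size is 200/(1 − r²).

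| r (assumed) | variance ratio 1 − r² | adjusted half-width (SD) | raw CI wider by | equivalent N |
|---|---|---|---|---|
| 0.3 | 0.91 | 0.264 | 5% | 220 |
| 0.5 | 0.75 | 0.240 | 15% | 267 |
| 0.7 | 0.51 | 0.198 | 40% | 392 |

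**Chance imbalance.** The standard error of the T0 difference between arms is also √(2/100) = 0.141 SD. A one-standard-error imbalance moves the raw follow-up difference by r × 0.141, which is 0.042, 0.071 or 0.099 SD at r = 0.3, 0.5 or 0.7. Adjustment removes this shift.

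**Carry-over to the metrics.** With benefit B and intervention cost C, net benefit is B − C, BCR is B/C and ROI is 100 × (B − C)/C. For a fixed C, each is linear in B, so the relative widening of the interval is the same for all three.

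**Secondary check on the horizon.** If the 2-week rule applies to the TiC-P, the windows after randomisation are about weeks 5–7 and 11–13. That is 2 + 2 = 4 weeks of about 13, or 4/13 = 31%, leaving 9 weeks unobserved. The article does not say which assessments enter the benefit, what period is totalled, or whether windows are scaled.

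**The case against.** The strongest reply is that randomisation makes the raw difference unbiased. Chance imbalance is then ordinary sampling error, which the bootstrap intervals reflect, and the Discussion already concedes weak economic power. At r = 0.3 the gain from adjustment is only 5%. The lack of bias stands in full: this is a matter of efficiency, not validity. It does not remove the point, because a valid interval can still be needlessly wide.

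It can also be said that the TiC-P is listed among the secondary outcomes, so the covariance analysis may be meant to cover it. That is possible for a test of TiC-P scores. The benefit entering the three metrics, however, has its own definition, and that definition is a plain subtraction.

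A reader might infer something stronger: that the benefit counts only 4 of 13 weeks while the whole programme cost is charged, so that a constant saving is understated 13/4 = 3.25-fold. The documents do not support this. Nothing says the windows would be summed without scaling, and nothing says the full programme cost is set against them; the intervention cost is treated as uncertain and varied in sensitivity analyses. A condensed article may leave the totalling rule to the full protocol or SAP. The 2-week rule itself is weak ground here: it is a blanket sentence that, read literally, would also cover personality traits and locus of control, and the TiC-P asks about monthly salary.

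**Conclusion.** The point holds as one of lost precision. The stated benefit formula does not use the T0 TiC-P cost that the trial collects, in contrast with the baseline-adjusted clinical analysis. The cost is an interval about 5% to 40% wider for an assumed correlation of 0.3 to 0.7, with exposure to chance baseline imbalance in net benefit, BCR and ROI. The range rests on 100 analysed per arm, a linear baseline relation and correlations the article does not supply; the T0 and follow-up data will show the actual value. No bias is claimed.

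The horizon is a secondary point and conditional. If recall is 2 weeks, costs are observed for about 31% of the 3 months, and benefit and intervention cost need a common horizon. That the plan would fail to do this is not established.

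**What to change.** Within each of the 2,500 bootstrap replicates, regress post-randomisation TiC-P cost on arm and T0 TiC-P cost. Take the adjusted arm difference as the benefit, and derive net benefit, BCR and ROI from it. Report the unadjusted difference alongside as a sensitivity result. The T0 data are already scheduled, so the cost is a few lines of analysis code, and the change should be fixed before the arms are compared.

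Also state the TiC-P recall period, the costing period, and how the observed windows are scaled or interpolated to the horizon over which the intervention cost is counted. Interpolation assumes roughly linear change between windows, and that assumption should be stated. Changing the questionnaire's recall period is not advisable: recruitment began in April 2017, so a change would mix recall periods across participants.
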